### **4.5.3. Safety Criteria for Adjustment or Stopping Doses**

Enrollment and treatment will be temporarily stopped if any of the following occur:

- DLT(s) defined as follows: two Grade 4 DLTs or single Grade 4 neurological toxicity or single Grade 3 or higher GVHD as DLT
- Any toxicity that is unexpected, significant, and unacceptable (based on SMC review and discussion), e.g., any occurrence of GVHD Grade 3 or higher
- Any death that occurs within 30 days of agenT-797 administration, except cases reported as related to the primary disease (COVID-19 or influenza)

If any of the above stopping criteria are met, an SMC meeting will occur to review the information and to recommend how to proceed.

The SMC will review any cohort under evaluation as well as the safety of all cohorts. All toxicities, including those outside the 14-day DLT period, will be evaluated. The SMC will make recommendations regarding any changes in study conduct ([Section 8.2](#)).

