### **4.5.1. Dose-Limiting Observation Period**

A minimum of 3 patients will be enrolled in each cohort, and the DLT observation period will be 14 days for each patient. Patients will continue to be monitored post-DLT period throughout the study. The totality of the safety data will be factored in by the SMC in the decision-making to move to enrollment of Cohort 2.

If a DLT occurs in 1 of the 3 patients during the DLT period, the cohort will be expanded to a total of 6 patients; if a DLT occurs in  $\geq 2$  patients in the total cohort of 6 patients, the MTD will be deemed to be exceeded, and that dose will not be escalated. The prior dose level will be evaluated to then proceed into the Expansion Cohort. The interval between patients in each cohort is at least 7 days with a 14-day interval between each cohort ([Section 4.4](#)).

The dose of agenT-797 will be escalated if none of the first 3 evaluable patients enrolled has a DLT based on SMC evaluations of data. If a cohort was expanded to include a total of 6 evaluable patients and no DLT occurs in the additional 3 patients, then the dose will be escalated based on the SMC evaluation of data.

After Amendment 7, the SMC will monitor safety on an ongoing basis.

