### **4.5.2. Maximum Tolerated Dose**

If a DLT occurs in  $\geq 2$  patients in a cohort, the MTD will be deemed to be exceeded, and the prior dose level will be evaluated to determine the MTD by increasing enrollment to 6 patients. If the prior dose level was already deemed to be safe and enrolled 6 patients, then it will be defined as the MTD. Dose Escalation will continue until the MTD is reached or the maximum planned dose level is shown to be safe. If none of the first 3 evaluable patients enrolled at the maximum planned dose experience a DLT, an additional 3 patients may be enrolled for a total of 6 patients at the maximum planned dose. Additional patients may also be enrolled in other lower dose cohorts.

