#### **4.12. ENROLLMENT STOPPING RULES**

Enrollment may be temporarily stopped if any of the following occur:

- A DLT (see [Section 8.1.4](#))
- Any toxicity that is unexpected, significant, and unacceptable (based on SMC review; [Section 8.2](#))
- Safety stopping rules ([Section 4.5.3](#))
- Documented Sponsor decision

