### 8.1.4. Dose-Limiting Toxicity Criteria

The DLT observation period is defined as 14 days after infusion of agenT-797. The nature, frequency, time to onset, severity of toxicities, medical history, and concomitant medication, as well as the success of standard medical management, will be analyzed to determine if a given toxicity should be considered a DLT by the SMC per charter.

A DLT is defined as any of the following at least possibly related AEs graded using NCI-CTCAE v5.0:

- General:
  - Any Grade 4 or 5 toxicity
- Hematologic:
  - Any Grade 3 hematologic toxicity that lasts for more than 7 days despite treatment

- Non-hematologic:
  - Any Grade 3 non-hematologic toxicity that lasts for more than 72 hours despite adequate treatment
  - Exceptions: Grade 3 events with a different definition of duration that are considered DLTs are the following:
    - Grade 3 renal or hepatic toxicity that lasts 7 days or longer
    - Any Grade 3 or higher toxicity that is cardiac, respiratory, or neurologic of any duration
- Immune:
  - Any Grade 2 acute GVHD that requires steroid therapy for > 7 days or that has progression of clinical signs and symptoms after 3 days of steroids or that has partial response after 14 days of treatment, or GVHD Grade 3 or higher
  - Any **new** Grade 3 CRS lasting more than 72 hours and/or **new** Grade 4 CRS of any duration at least possibly related to agenT-797. For patients presenting with Grade 2 or 3 CRS at baseline, worsening of baseline CRS grade, judged as at least possibly related to agenT-797, and occurring within 4 hours of infusion ([Lee 2019](#))
  - Any clinically significant Grade 3 autoimmune disorder that lasts for more than 72 hours at Grade 3 despite adequate treatment or any Grade 4 autoimmune disorder of any duration

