### **9.3. CRITERIA FOR THE TERMINATION OF THE STUDY**

No statistical stopping rules will be formulated for this study.

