### 3.8 Safety Criteria for Adjustment or Stopping Doses

Enrollment and treatment will be temporarily stopped if any of the following occur:

- DLT(s) defined as follows: two Grade 4 DLTs or single Grade 4 neurological toxicity or single Grade 3 or higher Graft-versus-Host Disease (GVHD) as DLT
- Any toxicity that is unexpected, significant, and unacceptable (based on SMC review and discussion), e.g., any occurrence of GVHD Grade 3 or higher

- Any death that occurs within 30 days of agenT-797 administration, except cases reported as related to the primary disease (COVID-19 or influenza)

If any of the above stopping criteria are met, an SMC meeting will occur to review the information and to recommend how to proceed.

The SMC will review any cohort under evaluation as well as the safety of all cohorts. All toxicities, including those outside the 14-day DLT period, will be evaluated.

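### Protocol 4.5.3 and 4.12 give the same pause triggers different force, two Grade 3 DLTs reach the MTD-exceeded count without an automatic pause, and the rule for Cohort 4 is not stated

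*Combined protocol and SAP*

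**What the plan says.** Protocol 4.5.3 opens its list with "Enrollment and treatment will be temporarily stopped if any of the following occur". Its first trigger is "DLT(s) defined as follows: two Grade 4 DLTs or single Grade 4 neurological toxicity or single Grade 3 or higher GVHD as DLT". Two further triggers follow: an unexpected, significant and unacceptable toxicity as judged by the SMC, and a death within 30 days that is not reported as related to the primary disease. If any trigger is met, an SMC meeting follows. SAP 3.8 repeats the mandatory wording and the same first trigger: "DLT(s) defined as follows: two Grade 4 DLTs or single Grade 4 neurological toxicity or single Grade 3 or higher Graft-versus-Host Disease (GVHD) as DLT".

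Protocol 4.12 opens with "Enrollment may be temporarily stopped if any of the following occur". It lists a DLT as defined in 8.1.4, the unexpected-toxicity trigger again, the safety stopping rules of 4.5.3 by cross-reference, and a documented sponsor decision. The SAP has no counterpart to this section.

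Protocol 4.5.2 says that with DLTs in two or more patients in a cohort, "the MTD will be deemed to be exceeded, and the prior dose level will be evaluated to determine the MTD". It sets no grade and no cohort size. Protocol 4.5.1 and the synopsis tie the same count to a cohort of 6. SAP 3.6 and 3.7 repeat 4.5.1 and 4.5.2.

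Protocol 8.1.4 counts several Grade 3 events as DLTs, among them "Any Grade 3 or higher toxicity that is cardiac, respiratory, or neurologic of any duration".

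For Part 2, 4.5.1 adds: "After Amendment 7, the SMC will monitor safety on an ongoing basis". Section 9.3 says: "No statistical stopping rules will be formulated for this study". Table 2 gives Cohort 4 up to 15 patients at the same dose level as Cohort 3, and labels its escalation type 3+12 without explanation.

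**The concern.** There are two separate inconsistencies.

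The first is force and scope. The same triggers oblige a stop of enrollment and treatment in 4.5.3, and merely permit a stop of enrollment in 4.12. A site working from 4.12 could think it has discretion that 4.5.3 does not give.

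The second is the DLT count. The event that 4.5.2 treats as showing the dose is above the MTD need not be one that obliges anyone to pause or convene under 4.5.3. In Part 1 the ban on escalation gives the count some effect. Cohort 4 has no escalation step, and 4.5.1 and 4.5.2 do not say that enrollment at the current dose stops once the MTD is deemed exceeded.

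DLTs are part of the primary endpoint, and the synopsis gives further evaluation of safety as the purpose of Cohort 4. Investigators and the SMC should be able to read from the protocol what a second DLT in that cohort obliges them to do.

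**Working it through.** The plan states no error rate or operating characteristic for its pausing rules, so there is no figure to reproduce. The main check is to run the same events through each rule.

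| DLTs observed in one cohort | 4.5.2 count (two or more DLT patients) | 4.5.3 DLT trigger (mandatory) | 4.12, a DLT (optional, enrollment only) |
|---|---|---|---|
| Two patients, each with a non-GVHD Grade 3 DLT | Met (2 ≥ 2) | Not met (no Grade 4) | Met |
| One non-GVHD Grade 3 and one non-neurological Grade 4 | Met | Not met (one Grade 4) | Met |
| Two patients, each with a Grade 4 DLT | Met | Met | Met |

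The first two rows are the gap. The table assumes that the 4.5.2 count applies to the cohort in question.

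**How often the gap could arise.** The inputs are a cohort of 15 (Table 2), the two-patient count (4.5.2) and the two-Grade-4 trigger (4.5.3). Not in the documents, and therefore assumed: independent patients, one DLT grade per patient, a true DLT rate p of 0.33 or 0.20, and a share f of DLTs at Grade 4 between 0.2 and 0.5. All other triggers are ignored.

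Let K be the number of DLT patients, K ~ Bin(15, p), and G the number with a Grade 4 DLT, G ~ Bin(15, pf). Since K ≤ 1 implies G ≤ 1,

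P(K ≥ 2 and G ≤ 1) = P(G ≤ 1) − P(K ≤ 1).

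For p = 0.33, P(K ≤ 1) = 0.67^15 + 15 × 0.33 × 0.67^14 = 0.0025 + 0.0182 = 0.0206 (summed before rounding).
- f = 0.2, pf = 0.066: P(G ≤ 1) = 0.3591 + 0.3806 = 0.7397; difference 0.719.
- f = 0.5, pf = 0.165: P(G ≤ 1) = 0.0669 + 0.1982 = 0.2651; difference 0.244.

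For p = 0.20, P(K ≤ 1) = 0.0352 + 0.1319 = 0.1671.
- f = 0.2, pf = 0.04: P(G ≤ 1) = 0.5421 + 0.3388 = 0.8809; difference 0.714.
- f = 0.5, pf = 0.10: P(G ≤ 1) = 0.2059 + 0.3432 = 0.5490; difference 0.382.

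**Why the denominator needs stating.** Two DLT patients are 2/6 = 33% of a cohort of 6 but 2/15 = 13% of a cohort of 15. At an assumed 10% DLT rate, the chance of two or more is 1 − 0.5314 − 0.3543 = 0.114 in 6 patients and 1 − 0.2059 − 0.3432 = 0.451 in 15. The second figure matters only if the 4.5.2 count is meant to apply to Cohort 4, which the documents leave open.

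**The case against.** The case on the other side is substantial.

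- **Grade 3 DLTs are not ignored.** Section 4.12 makes any single DLT a ground for pausing enrollment, and the second trigger in 4.5.3 can reach repeated Grade 3 events on SMC judgement. Under 8.1.4 the SMC decides whether a toxicity is a DLT, so DLTs could not accumulate without its knowledge. Section 4.5.1 also sets at least 7 days between patients in each cohort. All of this stands. A reader might infer that two Grade 3 DLTs lead to no pause at all. The documents do not support that; what is missing is an automatic, mandatory one.
- **The two rules serve different purposes.** One selects a dose and the other halts urgently, so different thresholds are not in themselves a contradiction. That stands too, but the protocol does not explain the relation between them.
- **Obeying 4.5.3 also satisfies 4.12.** True, but the reverse fails: a site that uses the discretion in 4.12 and continues would breach 4.5.3.
- **The two-DLT rule may belong to Part 1 only.** It sits under the dose escalation criteria, its actions are escalation actions, 4.5.1 and the synopsis tie it to a cohort of 6, Part 1 is marked completed, and Part 2 is left to ongoing SMC monitoring. This is a reasonable reading. However, 4.5.2 speaks of a cohort without limit, and 4.5.3 has the SMC review any cohort under evaluation.
- **The SMC charter is a separate document.** It may hold the Cohort 4 rules. It would not remove the conflict between 4.5.3 and 4.12.

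**Conclusion.** The point holds in two parts, both from the text alone. First, 4.5.3 and SAP 3.8 make mandatory, for enrollment and treatment, what 4.12 makes optional, for enrollment only. Second, two non-GVHD Grade 3 DLTs meet the 4.5.2 count but not the DLT trigger in 4.5.3, so no automatic pause or SMC meeting follows from 4.5.3.

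A third matter is an omission: the protocol and SAP do not say whether the two-DLT rule governs Cohort 4, or what is decided after the first 3 of the 3+12.

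Two stronger readings go too far. One is that Cohort 4 can keep enrolling at a dose already deemed too toxic; that requires 4.5.2 to govern Cohort 4, which is not established. The other is that a tolerable dose would probably be declared too toxic in 15 patients; that rests on the same condition, and 0.45 at an assumed 10% rate is below even odds.

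The illustrative probabilities, 0.72 to 0.24 at a 33% DLT rate and 0.71 to 0.38 at 20%, rest on assumed rates and grade shares. They describe the two-Grade-4 trigger alone and are not the probability of no pause. They show that the gap need not be rare.

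**What to change.** Reconcile protocol 4.5.1, 4.5.2, 4.5.3 and 4.12 with SAP 3.6 to 3.8:

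1. Give the triggers shared by 4.5.3 and 4.12 one force (mandatory or optional) and one scope (enrollment, or enrollment and treatment).
2. Make the DLT count that exceeds the MTD and the DLT count that obliges an SMC meeting consistent under the 8.1.4 definition.
3. State which rule governs Cohort 4 and with what denominator, and what decision attaches to the first 3 patients of the 3+12. If the SMC charter already settles this, cite it.

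The choice of thresholds is for the sponsor and the SMC. The cost is protocol and SAP wording, with possibly an extra ad hoc SMC review during Cohort 4.

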#### **4.5.4. Criteria for Study Termination**

Study termination criteria are provided in [Section 9.3](#). End-of-Hospitalization (EOH) details are provided in [Section 4.5.7](#).

#### **4.5.5. Screening**

Written informed consent must be obtained prior to performing any protocol-specific Screening procedures to determine eligibility ([Section 4.6.1.1](#) and [Table 3](#)). The Screening procedures may be conducted within 4 days prior to agenT-797 administration.

#### **4.5.6. Treatment and Evaluation Period**

Eligible patients will be treated with agenT-797 on Day 1. Assessments will be obtained through Day 32 or until discharge from hospital as outlined in the Schedule of Assessments in [Table 3](#).

#### **4.5.7. End-of-Hospitalization**

A patient's discharge from hospital or death will be considered EOH (whichever comes first). The patient will be contacted regarding any serious adverse event (SAEs) and to confirm survival up to 6 months after hospitalization ([Section 4.9](#)).

### **4.6. STUDY PROCEDURES**

Study procedures and assessments are provided in [Section 4.16](#).

#### **4.6.1. Administrative Procedures**

##### **4.6.1.1. Informed Consent**

The Principal Investigator or qualified designee (a duly appointed health care proxy with authority to consent) must obtain documented informed consent from each patient, or legal representative, prior to participating in the clinical trial ([Section 4.7.1](#)). A signed and dated informed consent form (ICF) must be received and documented prior to initiation of any study procedures. The ICF will adhere to Institutional Review Board (IRB)/Independent Ethics Committee (IEC) requirements, applicable laws and regulations, and Sponsor requirements.

**Table 3: Schedule of Assessments**

| Assessment                               | Screening      | Treatment Period             |   |   |   |   |        |                     |                     |                     |                        | EOH a | 30-Day F/U |
|------------------------------------------|----------------|------------------------------|---|---|---|---|--------|---------------------|---------------------|---------------------|------------------------|------------------|------------|
| Study Day                                | ± 4            | 1                            | 2 | 4 | 6 | 7 | 10 ± 1 | 14 ± 1 b | 21 ± 2 b | 28 ± 2 b | 32 to EOH b | Day of discharge | 30 ± 2     |
| Informed consent                         | X c |                              |   |   |   |   |        |                     |                     |                     |                        |                  |            |
| Inclusion/exclusion                      | X c |                              |   |   |   |   |        |                     |                     |                     |                        |                  |            |
| HLA serotype                             | X c |                              |   |   |   |   |        |                     |                     |                     |                        |                  |            |
| Medical history & demographics           | X c |                              |   |   |   |   |        |                     |                     |                     |                        |                  |            |
| Physical examination d        | X c | Daily monitoring/assessments |   |   |   |   |        |                     |                     |                     |                        | X                | X          |
| Vital signs e                 | X c | Daily monitoring/assessments |   |   |   |   |        |                     |                     |                     |                        | X                | X          |
| ECG f                         | X c | X                            |   |   |   |   |        |                     |                     | X                   |                        | X                | X          |
| Radiological evaluation (X-ray/CT)       | X c | X                            |   |   |   |   |        |                     |                     |                     |                        | X                |            |
| Concomitant medications & procedures     | X              | Continuously collected       |   |   |   |   |        |                     |                     |                     |                        |                  |            |
| Adverse events g              | X              | Continuously collected       |   |   |   |   |        |                     |                     |                     |                        |                  |            |
| Hematology h                  | X c | Daily monitoring/assessments |   |   |   |   |        |                     |                     |                     |                        | X                | X          |
| Coagulation h                 | X c | X                            |   | X |   | X | X      | X                   | X                   | X                   |                        | X                | X          |
| Clinical chemistry h          | X c | Daily monitoring/assessments |   |   |   |   |        |                     |                     |                     |                        | X                | X          |
| Urinalysis i                  | X c | X                            |   | X |   | X | X      | X                   | X                   | X                   |                        | X                | X          |
| Pregnancy test (WOCBP) j      | X              |                              |   |   |   |   |        |                     |                     |                     |                        |                  |            |
| Serum for cytokine analyses k | X c | X                            |   | X |   | X | X      | X                   | X                   | X                   |                        | X                |            |

| Assessment                                                                            | Screening      | Treatment Period                       |   |   |   |   |        |                     |                     |                     |                        | EOH a | 30-Day F/U |
|---------------------------------------------------------------------------------------|----------------|----------------------------------------|---|---|---|---|--------|---------------------|---------------------|---------------------|------------------------|------------------|------------|
| Study Day                                                                             | ± 4            | 1                                      | 2 | 4 | 6 | 7 | 10 ± 1 | 14 ± 1 b | 21 ± 2 b | 28 ± 2 b | 32 to EOH b | Day of discharge | 30 ± 2     |
| Whole blood for persistence of agenT-797 (peripheral persistence)                     | X c | X l                         | X | X | X | X | X      | X                   | X                   | X                   |                        | X                | X          |
| Whole blood for cfDNA (tissue persistence)                                            | X c | X m                         | X | X | X | X | X      | X                   | X                   | X                   |                        | X                | X          |
| Bronchoalveolar lavage (iNKT cell presence and biomarker) k,n              | X c | X                                      |   | X |   | X | X      | X                   | X                   | X                   |                        | X                |            |
| Epithelial sampling by bronchial protected specimen brush (RNA analysis) o | X c | X                                      |   | X |   | X | X      | X                   | X                   | X                   |                        | X                |            |
| Serum for alloantibodies                                                              |                | X c                         |   |   |   |   |        | X                   |                     |                     |                        | X                |            |
| agenT-797 cell infusion                                                               |                | X                                      |   |   |   |   |        |                     |                     |                     |                        |                  |            |
| Arterial blood gas                                                                    | X              | Daily monitoring/assessments as needed |   |   |   |   |        |                     |                     |                     |                        | X                | X          |
| Symptoms of ARDS p evaluation (Berlin definition) q             | X              | Daily monitoring/assessments as needed |   |   |   |   |        |                     |                     |                     |                        | X                | X          |
| SOFA score r                                                               | X              | Daily monitoring/assessments as needed |   |   |   |   |        |                     |                     |                     |                        | X                |            |
| Viral burden assessment (swab), or endotracheal suction as feasible (RT-PCR)          | X s | X                                      | X | X | X | X | X      | X                   | X                   | X                   |                        | X                |            |
| Viral shedding assessment as feasible                                                 |                | X                                      |   |   |   |   |        |                     |                     |                     |                        | X                |            |
| D-dimer, CPK, cardiac troponins, and ferritin                                         |                | Every 12h, as feasible                 |   |   |   |   |        |                     |                     |                     |                        | X                |            |

Abbreviations: AE: adverse events; AESI: adverse events of special interest; ARDS: acute respiratory distress syndrome; d: day(s); cfDNA: cell free DNA; CPK: creatine phosphokinase; CT: computed tomography; ECG: electrocardiogram; EOH: End-of-Hospitalization; F/U: Follow-up; HLA: human leukocyte antigen; h: hour (s); IL: interleukin; iNKT cells: invariant natural killer T cells; RT-PCR: reverse transcriptase polymerase chain reaction; SAE: serious adverse event; SOFA: sequential organ failure assessment; WOCBP: women of childbearing potential.

- a End-of-Hospitalization is defined as patient discharge from hospital and/or death. If a patient is discharged at Day 30, 30-day Follow-up will be the same as EOH. After discharge, a patient will enter Safety Follow-up period and the patient will be contacted by telephone 3 and 6 months after discharge regarding any SAEs and to confirm survival, as feasible. See [Sections 4.9 and 4.10](#).
- b In case of earlier discharge from the hospital, no visit is expected until 30-Day Follow-up.
- c Performed before infusion of agenT-797 on D1. These samples will be obtained at the time of the routine labs blood draws.
- d A complete examination, as feasible, will be performed at Screening and symptom-directed and medically indicated physical examinations are done thereafter.
- e Vital signs include body temperature, heart rate, respiratory rate, systolic and diastolic blood pressure and are assessed by physician or nurse. On the day of infusion of agenT-797 (D1), measurements will be 15 min prior to infusion, and 15 min, 30 min, 1h, 2h, 3h, and 4h postinfusion.
- f ECG to be performed at Screening, Day 1 predose and EOH, 30-Day Follow-up, and at other times as clinically indicated.
- g Only AEs associated with study procedures and/or leading to withdrawal and all SAEs will be collected prior to study drug infusion. Patients are monitored for toxicities following infusion. All other AEs, SAEs, and AESIs will be collected as per [Section 8](#) and as defined in the Safety Follow-up period ([Section 4.10](#)).
- h Hematology/coagulation/clinical chemistry: Complete blood count with automated and/or manual differential will be collected daily, as feasible. Coagulation: activated partial thromboplastin time and international normalized ratio. Clinical chemistry: includes but not limited to albumin, alkaline phosphatase, alanine aminotransferase, aspartate aminotransferase, blood urea nitrogen, urea, calcium, chloride, C-reactive protein, creatinine, glucose, lactate dehydrogenase, magnesium, phosphate/phosphorus, potassium, sodium, total bilirubin, direct and indirect bilirubin, total protein, and beta-2-microglobulin and will be collected daily, as feasible. All will be collected at EOH and at 30-Day Follow-up.
- i Urinalysis: pH, ketones, specific gravity, bilirubin, protein, blood, and glucose. Will be done at the days indicated and at EOH and at 30-Day Follow-up.
- j Pregnancy testing for women of child-bearing potential: serum test at Screening.
- k Cytokines/biomarkers: D1 – preinfusion, end of infusion, and at 2, 4, and 8 hours postinfusion agenT-797, and as feasible thereafter. Cytokines for analysis may include but are not limited to: epidermal growth factor, eotaxin, fibroblast growth factor-basic, granulocyte-colony stimulating factor, granulocyte-macrophage colony stimulating factor, hepatocyte growth factor, interferon-alpha, interferon-gamma, IL-1 beta, IL-1 alpha, IL-1RA, IL-2, IL-2R, IL-3, IL-4, IL-5, IL-6, IL-7, IL-8, IL-9, IL-10, IL-12 (p40/p70) IL-13, IL-15, IL-17A, IL-17F, IL-22, IP-10, monocyte chemoattractant protein-1, MIG, MIP-1 alpha, MIP-1 beta, Regulated upon Activation, Normal T Cell Expressed and Presumably Secreted, tumor necrosis factor-alpha, vascular endothelial growth factor, and matrix metalloproteinase-9.
- l To be obtained 5, 15, and 30 min, and 1, 2, and 4 hours postinfusion.
- m To be obtained 2 hours postinfusion.
- n To be obtained in intubated patients if clinically indicated using microlavage techniques when possible.
- o To be obtained in intubated patients when possible.
- p Evaluations including physical examination and procedures required for lung injury score evaluation (chest X-ray, PaO2/FiO2 ratio, positive end-expiratory pressure, compliance, mL/cm H2O) as needed, including daily or more often until recovery ([ARDS 2012](#)).
- q As needed.
- r SOFA score will be calculated using results of the following tests: PaO2, FiO2, platelet count, need for mechanical ventilation, Glasgow Coma score, bilirubin, mean arterial pressure or use of vasoactive medications, creatinine, and diagnosis of COVID-19 ([SOFA](#)).
- s Patients must be SARS-CoV-2 or influenza positive at diagnosis; refer to [Section 4.7.1](#).

